## Abstract

**Background:**

In Germany, approximately half a million people are diagnosed with cancer annually; this can be traumatic and lead to depression, anxiety, and adjustment disorders necessitating psycho-oncological intervention. Value-oriented behavioural activation, adopted from depression psychotherapy, aims to provide structured support to help patients adjust their personal values, goals, and activities within the context of their changed life situation. This trial aims to evaluate the effectiveness of video-based value-oriented behavioural activation against German S3-Guideline-compliant aftercare for cancer patients dealing with psychological distress.

**Methods:**

This trial will use covariate-adaptive randomisation according to gender and type of tumour disease to assign participants to one of two study arms (value-oriented behavioural activation consisting of 12 manualised follow-up sessions delivered via video consultation vs. S3-Guideline-compliant aftercare comprising three supportive talks). Psychological strain, psychosocial distress, quality of life, work-related outcomes, fear of cancer recurrence, goal adjustment, satisfaction with the consultant-participant relationship, and rumination will be measured at baseline, twice during treatment, posttreatment, and at the 6-month follow-up. The target sample of 146 tumour patients experiencing high psychosocial distress will be recruited at the Rehazentrum Oberharz, Germany.

**Discussion:**

This trial aims to test the effectiveness of value-oriented behavioural activation in aftercare for tumour patients, focusing on its capacity to reduce distress and the potential for long-term effects evaluated through a 6-month follow-up. The study’s possible challenges include enrolling a sufficient sample and ensuring adherence to treatment, mitigated through in-person recruitment and rigorous training of staff. If successful, the results will be of high public health relevance, especially for psychotherapeutic care in rural areas and among patients with limited mobility considering the video-based approach of the trial.

**Trial registration:**

This study was registered at the German Clinical Trials Register: DRKS00031900 on Sep 19, 2023.

**Supplementary Information:**

The online version contains supplementary material available at 10.1186/s13063-024-07953-w.

## Background

In Germany, every year approximately half a million people are newly diagnosed with cancer [1]. A diagnosis of a tumour disease can be regarded as a potentially traumatic event [2]. In some cases, a psychological impairment develops that meets the criteria for a mental disorder. Prevalence estimates for these resulting mental disorders, such as depression (up to 58 %), anxiety disorders (up to 49 %), and adjustment disorders (up to 52 %) vary depending on the type of tumour disease and the associated functional limitations and pain as well as the stage of the disease [3, 4]. Therefore, according to the current German S3-Guideline [5], once an increased psychological burden has been identified, a psycho-oncological intervention should be offered.

Currently, very unspecific, nonsystematic psycho-oncological interventions are offered in Germany [6]. These interventions have achieved moderate short- and medium-term effects on self-reported anxiety, depression, and quality of life [7]. Unspecific techniques (e.g. psycho-educational information and relaxation techniques) do not guarantee individual adaptation to the needs and requirements of persons with tumour disease. Especially when facing a potentially life-threatening disease, highly individualised needs will be involved, and those affected will have to adapt their goals, especially with a shortened life expectancy. Individualised goal-value-clarification and adaptation of treatment to these can be found in various treatment manuals for affective disorders [8], but these interventions have not yet been employed for psycho-oncological treatment [7]. It has been shown that successful detachment from goals that have become unattainable and a stronger focus on attainable goals are positively associated with the well-being of patients with tumours [9]. Manualised value-oriented behavioural activation may be a solution and result in better short- and long-term effects regarding anxiety, depression, and quality of life.

According to a meta-analysis [10], various approaches to value-oriented behavioural activation (VA) for individuals with depressive disorders proved to be at least equivalent to the conventional approach of cognitive-behavioural treatment of depression. A randomised controlled trial showed that VA also leads to a clinically significant reduction in depressive symptoms and perceived physical limitations and an improvement in quality of life and level of functioning in patients with breast cancer and an acute depressive episode [11]. Furthermore, this form of VA can promote the restoration of a sense of control in patients through its explicit reference to personal values and the resulting behavioural reinforcement [12]. Although previous research on VA in tumour diseases has been conducted predominantly with female patients with breast cancer, initial findings indicate that VA is an effective intervention for other oncological target groups [13].

VA is established for the treatment of depression [10] by clarifying personally important values and life goals against the background of a changed life situation and in (re)orienting everyday life accordingly. A detailed description of VA is available in a German-language manual for depressive disorders [14]. Applying a value-oriented approach borrowed from depression treatment to psycho-oncological care enables highly individualised treatment.

Current psycho-oncological interventions require participants to be motivated, mobile, and, above all, physically able to see consultants on an outpatient basis. This cannot be considered true for all participants, especially since oncological treatment is often accompanied by a number of persistent side effects such as pain, fatigue, and sleep disorders [15]. By using a video consultation, it can be ensured that participants and consultants communicate synchronously and that participants receive support in coping with everyday life despite these challenges.

The present study aims to assess the effectiveness of video-based, value-oriented behavioural activation (in the VA-V group) in comparison to German S3-Guideline-compliant outpatient aftercare (in the guideline group) in a randomised controlled trial. The primary objective is to evaluate whether the VA-V results in lower levels of distress (i.e. depression and anxiety scores on the HADS). The secondary objectives are to evaluate whether the VA-V (1) improves ability level and quality of life, (2) improves goal adjustment, (3) yields sufficient levels of treatment satisfaction and working relationships in a process evaluation, and (4) is affected by background factors (e.g. disease prognosis) in its influence on primary and secondary outcomes.

## Methods/design

### Trial design

This study is a nonblinded two-armed parallel randomised controlled trial (see Additional File 1 for the SPIRIT checklist). The superiority of the VA-V over the German S3-Guideline-based intervention will be evaluated. Participants will be randomly assigned to either the VA-V group or the German S3-Guideline-compliant aftercare group. Random allocation will be performed on a 1:1 ratio basis and covariate-adaptively for gender and type of tumour disease. The assessments will be conducted at baseline (T1), during the intervention (T2, T3), postintervention (T4), and at the 6-month follow-up (T5; see Fig. 1). The VA-V group will receive 12 online intervention sessions. The control group will be an active control group receiving 3 supportive online talks according to the German S3-Guideline [5].

**Fig. 1 Fig1:**
[figure not shown]
Trial flow diagram

### Participants, interventions, and outcomes

#### Study setting

Participants will be recruited at the Rehazentrum Oberharz Clausthal-Zellerfeld, Lower-Saxony, Germany, a clinic specialising in the rehabilitation of cancer patients (with the exception of lung cancer, cancers of the head and neck area, brain tumours and cancers of the nervous system). The sponsor of Rehazentrum Oberharz is the Deutsche Rentenversicherung (German pension insurance).

#### Eligibility criteria

The inclusion criteria will be the presence of an oncological disease (irrespective of type or prognosis; C00-D48), experiencing high psychosocial distress (defined as $$\ge 5$$ on the National Comprehensive Cancer Network (NCCN) Distress Thermometer [16]), and having a mental disorder according to the International Statistical Classification of Diseases and Related Health Problems (ICD-10 [17]). Correspondingly, individuals with the following diagnoses according to the ICD-10 will be included: unipolar depressive disorders (F32 – F34), anxiety disorders (F40, F41), stress-related and somatoform disorders (F42, F43, F45, F48.0), obsessive-compulsive disorders or adjustment disorders (F43.2), and nonorganic sleep disorders (F51). The minimum age will be 18 years, the maximum age will be 75 years. Participants will need to have sufficient knowledge of the German language to participate in the study, be able to give consent (e.g. persons under guardianship cannot participate), and have provided written informed consent (incl. consent to videography for quality assurance).

The exclusion criteria will be bipolar disorders (F31), schizophrenia and other delusional disorders (F20-F29), substance disorders (F10-19), and eating disorders (F50) because these disorders cannot be regarded as a consequence of the tumour disease in a narrow sense and require disorder- and symptom-specific therapeutic techniques which cannot be provided within the manualised VA-V intervention. Current or planned psychotherapeutic treatment will also be an exclusion criterion because this could represent a confounder in the evaluation of the intervention effect.

#### Interventions

*VA-V intervention.* Participants in the VA-V will receive twelve manual-based 50-minute sessions of video-based value-oriented behavioural activation, usually once a week, offered by a trained consultant. The trained consultants will be randomly assigned to the participants. However, due to holidays, illness, or other appointments, there may be 2–3 weeks between two appointments. Both the VA-V and the German S3-Guideline-based intervention will be offered by the same consultants to minimise person effects. If an appointment has been missed, efforts will be made to contact the participant to schedule a new appointment. If a participant wishes to discontinue the intervention, participants will be asked for their reasons. Discontinuations and all deviations of the intervention protocol will be documented.

To ensure treatment integrity and adherence to the intervention protocol, the intervention will be carried out by specially trained scientific staff (psychologists and pedagogues) of the Department of Clinical Psychology and Psychotherapy based on the VA-V manual and supervised by a psychological psychotherapist. Training and supervision will be provided by the author of the VA-V manual (CH), a psychological psychotherapist. In addition, it is planned that the conducting scientific staff will participate in a specific curriculum for psycho-oncological qualification―the advanced training in psychosocial oncology (Weiterbildung Psychosoziale Onkologie) certified by the German Cancer Society―during the project period. In the VA-V condition, all sessions will be video-graphed. The videographies will be used for quality assurance in terms of treatment integrity and supervision and―if the participants separately consented―for anonymised analysis of specific session parts (e.g. a thought experiment).

Video sessions will be implemented through the video conferencing tool RED connect (RED Medical Systems GmbH). This is a secure, end-to-end encrypted communication platform specifically designed and approved for the medical-therapeutic field. Data exchange (encrypted several times) is realised exclusively between consultants and participants (peer-to-peer connection). In the following, the 12 intervention sessions are described. *Introduction and anamnesis.* In the first session, the consultant and the study will be introduced, and relationship building, clarifying the organisational framework, and anamnesis of life and medical history will be conducted.*Feedback on diagnostic assessments and psychoeducation.* The most important results of the diagnostic assessments will be discussed with the participants. Myths about cancer as well as associated hopes (e.g. the feeling of being able to gain control if cancer can be influenced by positive thinking) and costs (e.g. the feeling of being to blame for one’s own illness) will be disputed. Furthermore, the extent to which current psychological distress is a consequence of the disease and the treatment or its side effects will be explored via psychoeducation.*Value-goal clarification and introduction to values and the value questionnaire.* The concept of values in life (according to Acceptance and Commitment Therapy [18]) will be introduced. This will be followed by an exploration of the participants’ own values before the cancer diagnosis and after the diagnosis and treatment (importance rating from 1 to 10); changes in values will be discussed.*Elaboration of old and new values, goal 1.* In this session, the most important life values will be selected by the participants. This will be followed by elaboration of the previous status or situation before the diagnosis and assessment of goals and activities based on the current life situation according to a three-colour scheme (green for current and possible goals/activities, red for goals/activities that are irretrievably blocked or no longer important, yellow for goals/activities that are no longer possible in the previous implementation or whose priority has decreased in comparison to before). New goals and activities will be developed, and value-based activities will be planned.*Elaboration of old and new values, goal 2.* Like in the last session, more important value areas will be elaborated, and value-based activities will be planned.*Elaboration of old and new values, goal 3, thought experiment.* Like in the last two sessions, more important value areas will be elaborated, and value-based activities will be planned. Additionally, a thought experiment will be conducted. Participants will be asked to imagine that they only have 6 months to live. It will then be elaborated how they would like to use their time with regard to the selected areas of life, values, goals, and activities (i.e. would there be differences/changes in priorities?).*Value-based behavioural activation, further activity building, and dealing with problems.* Barriers to the implementation of activities will be collected. Value-based activities will be planned (with special attention given to the activating amount of activities).*Completing the individual activity plan.* Exhaustion or fatigue syndrome, as a special barrier to the implementation of activities, will be discussed. From this, concrete changes for everyday life will be derived. Additionally, dealing with the avoidance of anticipated consequences will be a focus topic. The short- and long-term consequences of avoidance behaviour will be determined. Subsequently, corresponding activities that have been avoided thus far will be planned.*Dealing with specific problems, problem-solving training 1.* Problem-solving training will be introduced. First, it will involve a problem and goal definition. Second, possible solutions will be developed regardless of how unusual they are. Third, these possible solutions will be evaluated. Fourth, the best possible solution will be chosen. The fifth step will be to plan the concrete implementation of this possible solution.*Problem-solving training 2.* In the sixth step of the problem-solving training, solution attempts since the last session will be reviewed and evaluated. Sessions 10 and 11 will be designed according to the individual problems/symptoms of the participant. Either further problem-solving training, dealing with rumination, or dealing with fear of cancer recurrence will be the focus topics of these sessions. Dealing with rumination will include defining rumination and identifying it as an unfavourable coping strategy. Positive and negative meta-thoughts, dealing with trigger thoughts and rumination suspension will be disputed. Dealing with the fear of cancer recurrence will include defining fear of cancer recurrence and identifying positive meta-thoughts, which will then be disputed. The acceptance of unpleasant feelings and the reduction of safety/avoidance behaviour will be used as strategies.*Problem-solving training 3.* The session will be conducted according to the problem focus of the participant and can include either further problem-solving training or dealing with rumination or fear of cancer recurrence.*Closing session, summary, relapse prevention.* The various main topics of the intervention (clarification of values and goals, development of value-oriented activities, problem-solving, dealing with rumination and/or fear of cancer recurrence if necessary) will be summarised and reflected upon. An emergency plan will be developed.

*German S3-Guideline-based intervention.* Participants in the active control group will receive aftercare according to the German S3-Guideline ‘Psycho-oncological diagnosis, counselling and treatment of adult cancer patients’ [5]. They will receive three supportive talks at roughly the same times as the intervention group will receive sessions 1, 6, and 12. Supportive talks will cover fatigue management and relaxation techniques.

The German S3-Guideline-based intervention will thus involve more comprehensive aftercare than care as usual (CAU), as large gaps in care exist in outpatient cancer counselling and in the provision of outpatient psycho-oncological and psychosocial services [19]. Many of the spatial planning regions in Germany are underserved or have a low coverage rate (54 % have a coverage rate < 50 %, 30 % have a coverage rate between 50 % and < 75 %) regarding outpatient psycho-oncological care [6].

#### Outcomes

Various empirically validated questionnaires will be used to collect the data. The participants will complete these questionnaires online on a survey portal (ViVA platform) specially designed for the study. The programming of the ViVA platform is based on LimeSurvey (https://www.limesurvey.org). The questionnaires themselves will be created in LimeSurvey, while the ViVA platform will enable a customised user interface for participants and research staff. For an overview of the study outcome measures, see Tables 1 and 2. Participants will be contacted via the channel they have chosen in advance (e-mail, SMS, or both).

**Table 1 Tab1:** Measurement points and intervention sessions

Measurement/intervention	Content
Baseline measurement (T1)	Po-Bado-KF, NCCN Distress Thermometer, HADS, FBK-R23, SF-12, EQ-5D-5L, ERA^b^, WAI-r^b^, GoalAdjust, FCR7, RRQ
Intervention session 1^a^	Introduction and anamnesis
Intervention session 2	Feedback on diagnostic assessments and psychoeducation
Intervention session 3	Value-goal clarification, introduction to values and the value questionnaire
Intervention session 4	Elaboration of old and new values, goal 1
Intermediate measurement 1 (T2)	GoalAdjust, RRQ, ZUF-8 (only VA-V), WAI-SR (only VA-V)
Intervention session 5	Elaboration of old and new values, goal 2
Intervention session 6^a^	Elaboration of old and new values, goal 3
Intervention session 7	Value-oriented activation, further activity building and dealing with problems
Intervention session 8	Completing the individual activity plan
Intermediate measurement 2 (T3)	GoalAdjust, RRQ, ZUF-8 (only VA-V), WAI-SR (only VA-V)
Intervention session 9	Dealing with specific problems, Problem-solving training 1
Intervention session 10	Problem-solving training 2
Intervention session 11	Problem-solving training 3
Intervention session 12^a^	Closing session, summary, relapse prevention
Post measurement (T4)	HADS, FBK-R23, SF-12, EQ-5D-5L ERA^b^, GoalAdjust, FCR7, ZUF-8 (only VA-V), WAI-SR (only VA-V), RRQ, Closing questionnaire
Catamnesis (6 months post intervention, T5)	HADS, FBK-R23, SF-12, EQ-5D-5L, ERA^b^, GoalAdjust, FCR7, WAI-r^b^, RRQ

^a^ At roughly similar time points the 3 supportive talks in the German S3-Guideline group are scheduled. Content and duration deviate from the intervention group

^b^ Only participants who are not retired due to ill health or old-age

**Table 2 Tab2:** Outcome measures

Measures	T1	T2	T3	T4	T5
Po-Bado-KF	x				
NCCN Distress Thermometer	x				
HADS	x			x	x
SF-12	x			x	x
EQ-5D-5L	x			x	x
FBK-R23	x			x	x
WAI-r^a^	x				x
ERA^a^	x			x	x
FCR7	x			x	x
GoalAdjust	x	x	x	x	x
WAI-SR (only VA-V)		x	x	x	
ZUF-8 (only VA-V)		x	x	x	
RRQ	x	x	x	x	x
Closing questionnaire				x	

The measures are listed in the order in which they are presented to the participants

^a^ Only participants who are not retired due to ill health or old-age

*Primary outcome:*

*Psychological strain.* Symptoms of general anxiety and depression will be assessed with the Hospital Anxiety and Depression Scale, German version (HADS-D) [20]. The 14 items (7 each for depresson and anxiety) will be rated on a four-point Likert scale.

*Secondary outcomes:*

*Psychosocial distress.* For the initial assessment, the German version of the NCCN Distress Thermometer [21] will be used as a measure of psychosocial distress. If participants meet the criterion on the NCCN Distress Thermometer, they will complete the Questionnaire on Stress in Cancer Patients (FBK-R23) [22] as a more specific measure. Twenty-three items indicate whether the problem currently applies (0 = *does not apply*) and to what extent (1 = *hardly at all* to 5 = *very strongly*). The items can be combined into one total score and five subscales (psychosomatic complaints, anxiety, information deficits, everyday restrictions, and social stress).

*Quality of life*. Health-related quality of life will be assessed using the short version of the SF-36 Health Survey, the Short Form 12 (SF-12) [23] and the 5-level EQ-5D version (EQ-5D-5L) [24]. The SF-12 comprises 12 items distributed across eight dimensions: general health perception (1 item), physical health (2 items), limited physical role function (2 items), physical pain (1 item), vitality (1 item), mental health (2 items), limited emotional role function (2 items), and social functioning (1 item). The items have different scale levels. A physical and a mental sum score can be calculated. The EQ-5D-5L covers mobility, self-care, usual activities, pain/discomfort, and anxiety/depression [24]. Each of these five dimensions has five levels of perceived problems (no problem, slight problems, moderate problems, severe problems, unable to/extreme problems). An index value will be derived from these profiles, allowing the calculation of quality-adjusted life years. Additionally, overall current health will be assessed on a vertical visual analogue scale (‘The best health you can imagine’ to ‘The worst health you can imagine’) [24].

*Work-related outcomes*. Using a short version of the Work Ability Index (WAI-r) [25], the ability to work will be assessed, and a prognosis can be made about the development of the ability to work in two years. For this purpose, the minimum standard of two items for recording absenteeism and work ability will be used. For self-efficacy expectations in relation to work, a German version of the Return-to-Work Self-efficacy Questionnaire [26]―the Expectations of Work (ERA) questionnaire [27]―will be used. It comprises eleven items (e.g. ‘I will be able to concentrate on my work’) with a six-point Likert scale ranging from 1 $$=$$
*totally disagree* to 6 $$=$$
*totally agree*. Work-related outcomes will be assessed only if participants are not retired (due to ill health or old-age).

*Fear of cancer recurrence*. A German version of the Fear of Cancer Recurrence 7 Scale (FCR7) [28] will be used to obtain information about the participants’ fear of disease recurrence. Participants will complete self-report measures of the FCR7 on the ViVA platform and the fear of cancer recurrence platform. This platform will serve as a follow-up measurement in which the participants will be asked daily about their fear of cancer recurrence (FCR) for a period of 10 days. The two data collection platforms (ViVA and FCR) will be independent of each other. The platform will technically and in terms of data protection be identical to the ViVA platform. The data sets will be linked via the code.

*Goal adjustment*. The Goal Adjustment Scale will be used to measure individuals ability to disengage from unachievable goals or to orient themselves towards new goals [29]. The 10 items will be be rated on a five-point Likert scale ranging from 1 = *not at all true* to 5 = *very true*. The two subscales, Goal Disengagement and Goal Reengagement, comprise four and six items, respectively.

*Satisfaction*. The German version of the Client Satisfaction Questionnaire (ZUF-8) [30] will be used to measure general satisfaction with the intervention. The eight items will be assessed on a four-point Likert scale ranging from 1 = *most unfavourable* to 4 = *most positive*. The working relationship between the consultant and the participant will be recorded with the German-language short version of the Working Alliance Inventory (WAI-SR) [31]. It will be completed by both the consultant and the participant at T2, T3, and T4. Satisfaction will be assessed only in the VA-V group.

*Rumination*. The German version of the rumination scale [32] of the Rumination-Reflection Questionnaire (RRQ [33]) will be used to obtain information about ruminative cognitive patterns, with 12 items on a 5-point scale measuring agreement.

*Baseline variables:*

*Sociodemographics.* Sociodemographic data (e.g. age, gender, and marital status) and basic medical data (e.g. time of diagnosis and tumour type/stage) will be collected according to the short form of the Psycho-Oncological Basic Documentation (PO-Bado-KF) [34].

*Diagnosis.* The Structured Clinical Interview for DSM-5, Clinician Version (SCID-5-CV) [35], a semistructured interview guide, will be used in a 2-h online diagnostic appointment that takes place in both study arms after the premeasurement but before inclusion in the study. Video-based interviews will be conducted by trained persons with at least a Bachelor’s degree in psychology, and the results will be documented in paper form. The diagnosing persons will be randomly assigned to the participants. The diagnosis made on the basis of the interview is then transferred to the ViVA platform by the diagnosing person. For quality assurance, diagnostic interviews will be videographed. A psychological psychotherapist will supervise the interviews.

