#### Blinding

Participants cannot be blinded to their allocation since psychosocial interventions are identified naturally for both patients and counsellors. Baseline assessment will be conducted prior to allocation to minimise possible bias.

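### At T2, T3 and T4 only VA-V participants rate their consultant and treatment immediately before the rumination scale, so the arms answer the RRQ in different question contexts

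*Protocol article*

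**What the plan says.** The protocol article, Outcomes, gives the instruments in two tables. Only Table 2 claims to show the survey order: "The measures are listed in the order in which they are presented to the participants". Its last five rows are GoalAdjust, WAI-SR, ZUF-8, RRQ and the closing questionnaire. WAI-SR and ZUF-8 are marked for the VA-V arm at T2, T3 and T4. The RRQ has no arm restriction and is taken at all five time points.

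The text agrees with the arm restriction: "Satisfaction will be assessed only in the VA-V group". Of the WAI-SR it says: "It will be completed by both the consultant and the participant at T2, T3, and T4". The RRQ is listed among the secondary outcomes; it "will be used to obtain information about ruminative cognitive patterns, with 12 items on a 5-point scale measuring agreement".

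Table 1 lists content by visit. At T2 and T3 it has "GoalAdjust, RRQ, ZUF-8 (only VA-V), WAI-SR (only VA-V"), with the RRQ ahead of the VA-V-only forms. At T4 it has "ZUF-8 (only VA-V), WAI-SR (only VA-V), RRQ, Closing questionnaire", with the RRQ behind them. Under Blinding: "Participants cannot be blinded to their allocation".

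**The concern.** A between-arm comparison of a self-report scale assumes that the scale is administered in the same way in both arms. Here one arm first answers questions about how good the consultant and the treatment are, and then turns to its own ruminative thinking. Respondents may tend to stay consistent with the judgement they have just given, or to contrast with it. They know their allocation, and in VA-V rumination can be a focus topic of the later sessions.

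Any such effect would be added to the arm difference on the RRQ at the visits concerned. Randomisation does not balance it, because it arises from the measurement procedure and not from who was allocated. Adjustment for the T1 score does not remove it, because the forms are absent at T1. A larger sample does not shrink it. At stake is the reading of the rumination result during and directly after treatment.

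**Working it through.** **Step 1: order by arm.** I took the Table 2 row order at each visit, deleted the VA-V-only rows for the control arm, and read off the form directly before the RRQ.

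| Visit | VA-V: form before RRQ | Control: form before RRQ | Same? |
|---|---|---|---|
| T1 | GoalAdjust | GoalAdjust | yes |
| T2 | ZUF-8 (after WAI-SR) | GoalAdjust | no |
| T3 | ZUF-8 (after WAI-SR) | GoalAdjust | no |
| T4 | ZUF-8 (after WAI-SR) | GoalAdjust | no |
| T5 | GoalAdjust | GoalAdjust | yes |

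The arms differ at three of the five RRQ assessments.

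**Step 2: which other outcomes are touched.** In Table 2 the HADS, SF-12, EQ-5D-5L, FBK-R23, ERA, FCR7 and GoalAdjust all stand above WAI-SR and ZUF-8. The restriction on ERA and WAI-r concerns retirement, not arm. Within a survey, the RRQ is therefore the only shared scale outcome that follows the arm-specific forms.

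**Step 3: form of the bias.** Let τ be the true standardised effect on the RRQ at one of these visits and δ the shift caused by the preceding forms in VA-V. The expected arm difference is τ + δ. At T2 to T4 form order and arm coincide completely, so the data from those visits cannot split the sum.

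**Step 4: illustration of size.** The documents give no value for δ, so every value here is an assumption. With τ = 0, a two-sided 5% two-sample t-test has 2n − 2 degrees of freedom and noncentrality δ·√(n/2). The per-arm sizes 51 and 73 come from the Sample size section.

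- n = 51: √(51/2) = 5.05, 100 degrees of freedom.
- n = 73: √(73/2) = 6.04, 144 degrees of freedom.

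| Assumed δ (SD) | Noncentrality, n = 51 | Rejects, n = 51 | Noncentrality, n = 73 | Rejects, n = 73 |
|---|---|---|---|---|
| 0 | 0 | 0.050 | 0 | 0.050 |
| 0.1 | 0.505 | 0.079 | 0.604 | 0.092 |
| 0.2 | 1.010 | 0.170 | 1.208 | 0.225 |
| 0.3 | 1.515 | 0.323 | 1.812 | 0.437 |

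These rates follow mechanically from the assumed shift. They belong to a single-visit t-test and not to the multilevel structural equation model in Statistical methods, so they are not this trial's error rates.

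**The case against.** The strongest case against is about weight. Rumination is one secondary outcome and appears in none of the objectives stated in the Background. The primary outcome precedes the arm-specific forms. Nothing in the documents shows that the shift is other than zero. Participants are unblinded and receive 12 sessions against 3 talks, so self-report already takes place in different circumstances, and two short forms may add little. All of this stands, and it limits the point to a cheap improvement. It does not answer it, because this difference, unlike the lack of blinding, can be removed.

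Several stronger readings are tempting but not supported:

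- *That a treatment effect on rumination cannot be identified at all.* The T5 comparison is made after the same forms in both arms and does not have this problem.
- *That the trial's main result is at risk.* HADS comes before the forms at T4 and is unaffected.
- *That the extra forms cause more break-off before the RRQ in VA-V.* The documents give no figure on break-off within a survey. They describe reminders after 3 and 6 days and maximum-likelihood handling of missing values; neither targets break-off, but neither suggests that it occurs.
- *That Table 1 confirms the order at T4, or contradicts Table 2 at T2 and T3.* Table 1 does not claim to show presentation order and departs from Table 2 elsewhere (FBK-R23 before SF-12, GoalAdjust before FCR7). It is neither confirmation nor contradiction, although two lists that differ are a reason to state one order.

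An analysis plan not shown here would not settle the matter. The article itself fixes the order, and analysis cannot undo it at T2 to T4.

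**Conclusion.** The point holds in limited form. By the only statement of presentation order in the article, the RRQ follows two VA-V-only forms in one arm and GoalAdjust in the other at T2, T3 and T4. The rumination comparison at those visits, including post-treatment, is open to an arm-specific order effect of unknown size and direction. The RRQ at T1 and T5, the HADS and the remaining shared outcomes are not affected.

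This rests on one assumption: that the platform presents the forms as the Table 2 note says. The asymmetry is then established, but the amount of bias is not. No stated figure, hypothesis or primary analysis is wrong. The change is worth making because it costs almost nothing and removes a measurement difference that cannot be repaired afterwards.

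**What to change.** Present WAI-SR and ZUF-8 after every instrument common to both arms: after the RRQ at T2 and T3, and after the RRQ next to the closing questionnaire at T4. State this single order in Tables 1 and 2. In the analysis file, flag any VA-V participants already surveyed in the old order. If the platform already shows the RRQ first, correcting the tables is enough.

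The cost is a change of page order in LimeSurvey and a table correction, with no added items, visits, staff or patients. The small downside is a mixed form order within VA-V for those already surveyed; the flag records the mixture but does not remove it. Their number is not in the documents. It should be small if the change is made early: consent began on 30 October 2023, protocol version 1.0 is dated 7 November 2023, and T2 follows the fourth of sessions that are usually weekly. For visits already collected in the old order, the T5 RRQ is the comparison free of this problem.
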